### Pharmacological treatment

In order to reduce the possible confounding effect of pharmacotherapy, both on clinical and neuroimaging measures, an adaptation of the APA Guidelines [1] will be adopted to harmonize the prescriptions. Briefly, it includes the following principles: 1) Treatment is symptom specific, directed at particular behavioral dimensions; 2) Affective dysregulation and impulsivity/aggression are risk factors for suicidal behavior, self-injury, and are given high priority in selecting pharmacological agents; 3) Medication targets both acute symptoms (e.g., anger treated with dopamine-blocking agents) and chronic vulnerabilities (e.g., temperamental impulsivity treated with serotonergic agents).

Symptoms to be targeted are divided in three groups: Affective dysregulation symptoms, Impulsive behavioral symptoms and Cognitive-perceptual symptoms and each of this has specific recommendation.

### Primary outcome

The primary outcome measure will be changes in emotion regulation, measured by the Difficulties in Emotion Regulation Scale (DERS) [36, 37]. This scale is a 36-item self-report questionnaire comprising a total score and six dimensions: (1) Non-acceptance of emotional responses (6 items); (2) Difficulties engaging in goal-directed behavior (5 items); (3) Impulse control difficulties (6 items); (4) Lack of emotional awareness (6 items); (5) Limited access to emotion regulation strategies (8 items); (6) Lack of emotional clarity (5 items). The scale showed good psychometric properties, in terms of internal consistency (Cronbach’s alpha between 0.80 and 0.93), construct and predictive validity and adequate test-retest reliability.

### Secondary outcomes

A multidimensional evaluation with standardized tools will assess secondary outcomes in several psychological domains.

Metacognition Assessment Interview (MAI) [33, 47, 48]. Metacognitive functions will be measured with the MAI, a semi-structured clinical interview aimed to evaluate the metacognitive abilities of patients. The interviewers ask for a report of an emotionally meaningful experience or life event occurred in the previous 6 months, in which the subject and another person was involved. After the spontaneous report of the situation, interviewers asked a series of specific questions designed to evaluate the four metacognitive subfunctions (monitoring, integration, differentiation, and decentration).

Symptoms Check-list 90 Revised (SCL-90-R) [49]. General psychopathology will be assessed with the SCL-90-R, a 90 item self-report inventory aimed to measure the presence of psychological symptoms. The SCL-90-R assessed nine symptom dimensions: (1) Somatization; (2) Obsessive–Compulsive; (3) Interpersonal Sensitivity; (4) Depression; (5) Anxiety; (6) Hostility; (7) Phobic Anxiety; (8) Paranoid Ideation; and 9) Psychoticism. For the purpose of our study, we will used the Global Severity Index (GSI), which is the mean value of all of the items, and is considered a measure of global symptomatic distress.

Beck Depression Inventory II (BDI-II) [50]. Depressive symptoms will be evaluated by the BDI-II, a 21-item self-report questionnaire measuring the severity of depressive symptoms in the past 2 weeks with higher scores correlating higher levels of depression.

State-Trait Anger Expression Inventory (STAXI) [51]. State and Trait anger will be assessed with STAXI-2, that is a 57-item inventory which measures the intensity of anger as an emotional state (State Anger) and the disposition to experience angry feelings as a personality trait (Trait Anger). The instrument consists of six scales measuring the intensity of anger and the disposition to experience angry feelings. Items consist of 4-point scales that assess intensity of anger at a particular moment and the frequency of anger experience, expression, and control.

Barratt Impulsiveness Scale (BIS) [52] is a questionnaire aimed to evaluated impulsiveness. The BIS-11 identifies three factors that express three different dimensions of impulsivity: Motor impulsiveness, Impulsivity without planning and Cognitive impulsivity and provides a general index of the construct, as a total score. These scales have shown a good reliability and validity with other measures of the same dimension and the total score of the BIS-11 is an internally consistent measure of impulsiveness.

Interpersonal functioning will be assessed by Inventory of Interpersonal Problems (IIP) [53]. IIP is a 57 items self-report, evaluating different dimensions of interpersonal features (interpersonal sensitivity, interpersonal ambivalence, aggression, need for social approval, and lack of sociability).

Alexithymia will be measured by Toronto Alexithymia Scale (TAS-20) [54], a self-report consisting of 20 items rated on a 5-point Likert scale. TAS-20 provide a total score and three subscales: Difficulties Identifying Feelings; Difficulties Describing Feelings; and Externally Oriented Thinking, which refers to a specific tendency to focus on superficial matters and to avoid emotional thinking (Bagby, et al., 1994).

Childhood traumatic experiences will be evaluated by the Childhood Trauma Questionnaire (CTQ) [55]. The CTQ includes a 28-items that measures 5 types of maltreatment – emotional, physical, and sexual abuse, and emotional and physical neglect.

The attachment experience will be assessed by the Attachment Style Questionnaire (ASQ) [56] that is a 40-item survey that uses a 6-point Likert-type scale. The ASQ yields five factor scores: one is a factor representing secure attachment, the other four represent a particular aspect of insecure attachment.

Data on demographics, suicide attempts, self-injury and aggression episodes, hospitalizations, and pharmacotherapy will be collected.

At the baseline, the neuropsychological test battery included measures used to assess nonverbal reasoning (Raven’s Colored Progressive Matrices), verbal fluency (phonemic and semantic), visuospatial capacity (Rey–Osterrieth Complex Figure Copy), and attention and executive function (Trail Making Test, Wisconsin Card Sorting Test, Stroop Test), memory (Story Recall, Rey–Osterrieth Complex Figure Recall, Digit Span). All of the neuropsychological tests were administered and scored according to standard procedures [57].

Furthermore, all participants completed the Interpersonal Reactivity Index (IRI) [58], the Reading the Mind in the Eyes (RME) [59], the Facially expressed emotion labeling (FEEL) [60] and an experimental task to assess emotional priming (Emotional Priming Paradigm, EPP) [61].

Additionally, we will collect blood samples at baseline and at the different time of observation in order to explore possible peripheral biomarkers of emotional dysregulation and related to the limbic system, neuroplasticity, presence of inflammation and stress response and to observe modifications during treatment.

### Neuroimaging protocol

Structural, functional and diffusion MRI following the ADNI protocol [62] will be acquired in BPD patients twice, at the baseline and after treatment, in order to assess functional and structural brain changes after psychotherapy. Healthy volunteers (*N* = 30) will be scanned once for comparison of baseline data. Image acquisition will be performed on a 3 Tesla scanner with a 64 Channels RF HEAD COIL (Skyra Siemens, Erlangen, Germany) at the Unit of Neuroradiology – Spedali Civili Hospital (Brescia, Italy). In order to assess the cerebral patterns of activation in response to emotional visual stimuli, during fMRI scans (EPI sequence TR/TE 2000/30 ms, voxel size of 2.2 × 2.2 × 3.5 mm), participants will view unpleasant, neutral, and pleasant photographic pictures from the IAPS [63]. In particular, the fMRI study paradigm will be adapted from other studies [27, 64]. Briefly, a total of 96 intermixed unpleasant, neutral, and pleasant photographic images will be presented twice in a random order for a total of 192 trials [27, 64]. Participants will be instructed to watch the picture and then make a three-choice response (unpleasant, neutral, and pleasant) with their dominant hand, basing on the meaning for them personally. Lastly, in order to check that participants have properly understood the task, they will view the same 96 pictures immediately following the scan and will evaluated them using the Self-Assessment Manikin scale (9-point scale) [65].

### Sample size

We consider as primary outcome the DERS score and assume quite homogenous population in terms of DERS scores among the recruitment centers. Previous studies reported that the standard deviation (SD) of DERS was 20.7 in females and 18.8 in males [36]. Thus, we assumed a SD of about 20 points. In addition, the correlation between two evaluations (12 months apart) was expected around 0.7 (indicating that about 50% of the variance of the second measurement should be explained by the first measurement). We computed that the SD of DERS changes will be about 15. Our hypothesis is that MIT will decrease DERS more than SCM and, more precisely, a difference between MIT and SCM mean effect larger than 10 points will be considered clinically relevant. To recognize such difference as statistically significant (at bilateral alpha level of 0.05) with an adequate power (0.80), the total number of patients to be recruited should be 60, raised up to 80 (40 MIT + 40 SCM), considering an attrition rate around 20%.

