### Strengths and limitations

The main strength of the project is the synergy between clinical and biological expertise. Although psychotherapies are delivered in routine clinical settings, a dedicated research team coordinates and supports the activities of the project. The periodic supervision and the systematic assessment of fidelity delivered by the authors of the MIT is an effort to reduce variability and to maximize the treatment adherence. The multidimensional clinical assessment gives the opportunity to characterize BPD patients.

One possible limitation is represented by the presence (possible but not mandatory) of pharmacotherapy, which could have an impact both on clinical and neurobiological aspects. Although the pharmacotherapy does not represent the first choice in the treatment of BPD patients, it is well documented that pharmacotherapy is very common both in the United States and in Europe, with a percentage of patients prescribed medication ranging between 70% to more than 80% [68–70]. Furthermore, polypharmacy is also a common practice, with more than one-third of participants with BPD in these studies taking at least three drugs. One possible strategy to avoid that the presence of medication represents a potential confounding factor on clinical and neurobiological outcomes could be the enrollment of drug-naïve/free patients. On the one hand, this strategy could be potentially useful, on the other hand it would lead to include a group of patients that might not be representative of the clinical *real world* where BPD patients are commonly treated with pharmacotherapy. We will minimize this source of variability by using a standard methodology to prescribe pharmacotherapy [1]. Furthermore, the large number of subjects will allow us to conduct additional analyses on sub-groups of patients who were given similar treatments. Another critical aspect could be adherence to the psychotherapy, but in the definition of the sample size we considered an attrition rate of 20% to mitigate this problem, coherently with other similar study.

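### Sixty evaluable patients give about 69–72% power on the protocol's own inputs, not the stated 80%

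*Protocol article*

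**What the plan says.** The Sample size section sets out the whole calculation in one paragraph. The DERS is the primary outcome. For its spread at one time point: "Thus, we assumed a SD of about 20 points". The correlation between two evaluations 12 months apart is put at 0.7. From these: "We computed that the SD of DERS changes will be about 15". The target effect is given as: "a difference between MIT and SCM mean effect larger than 10 points will be considered clinically relevant". The test is set "at bilateral alpha level of 0.05" and "with an adequate power (0.80". The result is: "total number of patients to be recruited should be 60, raised up to 80 (40 MIT + 40 SCM), considering an attrition rate" of around 20%.

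Strengths and limitations, in the Discussion, relies on the same allowance when it addresses adherence to psychotherapy: "in the definition of the sample size we considered an attrition rate of 20% to mitigate this problem".

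**The concern.** All inputs are stated, so the sample size can be recomputed without outside information, and it does not come out at 60. Because 60 is then raised for attrition, it can only be the number of evaluable patients meant to deliver 80% power.

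This is the power claim for the primary outcome. If it is too high, the risk of missing a difference the protocol itself calls clinically relevant is larger than stated, and a non-significant result would be read against a power the design does not have. The step from 60 to 80 also does not match 20% attrition exactly, so the section does not make clear how many evaluable patients are expected.

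**Working it through.** **Inputs (all from Sample size):** SD 20 at one time point; correlation 0.7; SD of change about 15; difference 10; two-sided alpha 0.05; power 0.80; 1:1 allocation; 60 before attrition, 80 recruited; attrition around 20%.

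**1. SD of change.** SD × √(2(1 − r)) = 20 × √(2 × 0.3) = √240 = 15.49. The protocol carries forward 15. Both values are used below.

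**2. Trying to reproduce 60.** Normal approximation, per arm: n = 2(1.960 + 0.842)² × SD² / 10².
- SD 15: 2 × 7.849 × 225 / 100 = 35.3, so 36 per arm, 72 in total.
- SD 15.49: 2 × 7.849 × 240 / 100 = 37.7, so 38 per arm, 76 in total.

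With the exact (noncentral) t-test these become 37 per arm (74) and 39 per arm (78). Neither method gives 60.

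**3. Power for a 10-point difference, two-sided 5% t-test.** The noncentrality parameter is 10 / (SD × √(2/n)). At 30 per arm it is 2.58 for SD 15 and 2.50 for SD 15.49, against a critical value of 2.00 on 58 degrees of freedom.

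| Evaluable (per arm) | Change score, SD 15 | Change score, SD 15.49 | Baseline-adjusted, SD 14.28 |
|---|---|---|---|
| 60 (30) | 71.9% | 69.1% | 76.0% |
| 64 (32) | 74.7% | 72.0% | 78.7% |
| 80 (40) | 83.8% | 81.4% | 87.1% |

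The normal approximation adds only about 1.5 points at 60: 73.3% for SD 15 and 70.5% for SD 15.49.

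**4. Readings more favourable to the plan.**
- *Baseline adjustment.* The residual SD is 20 × √(1 − 0.49) = 14.28, or 20 × √0.5 = 14.14 if exactly half the variance is explained. These need 68 or 66 evaluable patients by t-test (66 or 64 by normal approximation). At 60, power is 76.0% or 76.8% by t-test.
- *One-sided 5%.* n = 2(1.645 + 0.842)² × 240 / 100 = 29.7 per arm, so 30 and 60 in total. This matches the stated figure, but only with the unrounded SD and the normal approximation, and it contradicts the two-sided alpha in the text. With SD 15 it gives 27.8 per arm, so 56 in total.
- *What 60 would require.* For 30 per arm to give 80% by two-sided t-test, the SD of change would have to be 13.6, that is a correlation of 1 − 13.6²/800 = 0.77.

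**5. Attrition.** 60 / 0.8 = 75. Going from 80 to 60 is a loss of 20/80 = 25%. Losing 20% of 80 leaves 64.

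**6. Difference detectable with 80% power on change scores.** At 60 evaluable it is 11.0 (SD 15) to 11.4 (SD 15.49) points. At 64 it is 10.7 to 11.0. All exceed the 10-point threshold.

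**The case against.** The best defence is that the trial recruits 80, not 60. With all 80 contributing, power on change scores is 81–84%. With 20% loss there are 64, and the shortfall at the protocol's own SD of 15 is about 5 points. The Statistical analyses section plans mixed models or GEE with imputation, so patients who drop out after the 6-month visit still contribute something, and adjusting for baseline at 64 evaluable brings power to about 79%. On that view, the 28–31% risk of a miss at 60 is not the expected risk for the trial as sized.

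This narrows the gap but does not close it. The section says that 60 delivers 80% power, and that is wrong under every two-sided reading tried. Imputation does not restore the information lost with missing outcomes, and the only SD the section carries into the calculation is that of the change score.

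Three further points have merit:
- Rounding 15.49 to 15 is within the looseness of the inputs and moves the total by only about 4. The error is already there at SD 15.
- Raising 75 to 80 is largely excused by the approximate attrition rate and by blocks of 4, which give 80 as 20 whole blocks. The attrition mismatch is therefore a minor point.
- A one-sided calculation as the source of the 60 is only an inference, since the document does not say so.

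**Conclusion.** The concern holds. On the stated inputs, 60 evaluable patients give 72% power (SD 15) or 69% (SD 15.49), and 80% power needs 74 or 78. At the 64 expected after 20% attrition, power is 75% or 72%. The chance of missing a true 10-point difference is thus 28–31% at 60 and 25–28% at 64, not 20%.

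These figures assume a two-sample t-test on 12-month change, equal arms, independent patients, and the protocol's SD and correlation. An analysis adjusted for baseline would bring 64 evaluable patients to about 79%, close to target, but the section does not base its calculation on one. The error is confined to the stated power and sample size. Randomisation and the type I error rate are not affected.

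**What to change.** Correct the Sample size paragraph. Suggested wording: *With 80 patients randomised and 20% attrition (64 evaluable), a 10-point difference in DERS change is detected at two-sided 5% with about 72% power on change scores (SD 15.5), or about 79% with adjustment for baseline; with 60 evaluable, the figures are 69% and 76%.* If the SD is kept at 15, the change-score figures are 75% at 64 and 72% at 60.

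State the attrition that 80 allows for: 25% if 60 is the evaluable target, otherwise 20% with 64 evaluable. Bring the sentence in Strengths and limitations into line. If the power claim is to rest on the baseline-adjusted analysis, say that this is the analysis being powered.

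The cost is a text correction and a less favourable power figure. It needs no additional patients and no change in conduct. The article reports that recruitment began in May 2015 and expects the study to end in November 2018, so the correction bears mainly on how the result is reported and read.

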### Randomization

After baseline assessments, eligible participants will be assigned to treatment arms using randomly generated block randomization scheme within each center. Considering the trade-off between the clinical best practices (e.g. The minimization of waiting list for patients) and rigorous statistical-methodological procedures, block size is fixed equal to 4. With this block size and the two arms (named 0,1), there are 6 different ways -type of blocks Bi- (as result of combination of 4 subjects into 2-element grouping) to allocate the patients: B1 [0011]; B2 [0101]; B3 [0110]; B4 [1010]; B5 [1001]; B6 [1100].

The 80 patients of the project will be randomly assigned to the two arms by a random choice (with replacing) of 20 blocks among the six blocks above defined. For the random choice, the ‘sample’ command of the statistical software R was used (sample (1:6, 20, replace = T)). Random allocation will be done by a statistician. Within 2 weeks, the clinician in charge for clinical evaluation will enrolled the patients and will communicate the experimental arms.

Given the nature of the psychological treatment neither the therapists nor the participants can be blinded for the delivered treatment.

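### A fixed block size of 4 in an open trial, with one clinician both enrolling patients and announcing arms, lets up to a third of allocations be foreseen

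*Protocol article*

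**What the plan says.** The Randomization section of the protocol article describes a "randomly generated block randomization scheme within each center" and adds that "block size is fixed equal to 4". It explains this as a compromise between clinical practice, such as short waiting lists, and statistical rigour. It lists all six balanced patterns of four and gives the R command used to draw them. A statistician carries out the random allocation. The section continues: "Within 2 weeks, the clinician in charge for clinical evaluation will enrolled the patients and will communicate the experimental arms". It also says that "neither the therapists nor the participants can be blinded for the delivered treatment".

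The same section opens by placing eligibility and baseline assessment before assignment to an arm. The Primary outcome section defines the outcome as change in DERS, a self-report questionnaire. The Sample size section plans 40 patients per arm and states the hypothesis that MIT lowers DERS more than SCM.

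**The concern.** When every block has the same small size and arms become known as treatment starts, the remaining places in a block can be worked out by counting. The fourth place is always determined, and the third is determined whenever the first two went to the same arm. The clinician who enrols patients and passes on the arms is well placed to keep that count.

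What is at stake is selection bias. A recruiter who foresees the next arm can delay, decline or bring forward a patient. The stated hypothesis favours MIT and the target difference is 10 DERS points in 80 patients, so steering even part of the predictable places could matter. DERS is measured before assignment, so an imbalance in baseline DERS would be visible and could be adjusted for. Selection on unrecorded features, such as motivation or expected attendance, would be neither visible nor adjustable.

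**Working it through.** **Inputs** (Randomization and Sample size sections): two arms, 1:1, block size 4, blocks drawn with equal probability, 20 blocks, 80 patients.

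**The plan's own figures.** Number of balanced blocks of 4: C(4,2) = 6, as stated. Patients covered: 20 × 4 = 80, as stated.

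**Allocations that are certain beforehand.** The observer is assumed to know the block size and all earlier arms at the centre, with patients allocated one at a time. A place is certain when one arm has already used both of its places.

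- Places 1 and 2: never certain.
- Place 3: certain if the first two arms match, which holds in 2 of the 6 blocks, so 1/3.
- Place 4: always certain.
- Per block: 0 + 0 + 1/3 + 1 = 4/3 of 4 places = 33.3%.
- Over the trial: 80 × 1/3 = 26.7 patients.

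**Success of the best guess** (choose the arm with more places left; toss a coin if equal).

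- Place 1: 1/2.
- Place 2: 2/3, since the other arm holds 2 of the 3 remaining places.
- Place 3: (1/3 × 1) + (2/3 × 1/2) = 2/3.
- Place 4: 1.
- Sum: 1/2 + 2/3 + 2/3 + 1 = 2.83 of 4 = 70.8%.

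**Alternatives.** Fixed sizes are enumerated exactly. Mixed sizes are simulated with 40 patients per centre (an assumed even split), each size equally likely, and an observer who knows the set of sizes but not which one is in use.

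| Scheme | Certain allocations | Best guess correct |
|---|---|---|
| Fixed 4 | 33.3% (26.7 of 80) | 70.8% |
| Fixed 6 | 25.0% (20 of 80) | 68.3% |
| Fixed 8 | 20.0% (16 of 80) | 66.6% |
| Random 4/6 | about 5.7% (80 × 0.057 = 4.6 of 80) | 68.9% |
| Random 4/6/8 | about 2.4% (80 × 0.024 = 1.9 of 80) | 67.6% |

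Varying the size removes most of the certainty but little of the advantage in guessing: 70.8% falls to 68.9% with a 4/6 mix, about 2 percentage points. Block size alone is therefore not a sufficient remedy.

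**Leaving out determined assignments.** 80 − 26.7 = 53.3, so about 53 patients would remain before any attrition. The Sample size section asks for 60.

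**The case against.** Centre-stratified blocks of 4 are conventional, and the article gives a reason for them. A statistician makes the allocation, and nothing says that the recruiting clinician holds the list, is told the block size or keeps a tally. Further concealment steps may stand in a fuller protocol. All of this stands, and it limits the claim to what the stated design permits.

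Three stronger readings are tempting, and the document does not support them.

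- **That the block size was disclosed to sites during enrolment.** The only disclosure shown is the article itself. Recruitment began in May 2015 and the study was expected to end in November 2018 (Trial status). A recruiter could infer a constant size of 4, but no text says that sites were told.
- **That patients are enrolled after their arm is known.** The sentence on the clinician can be read so, but the section opens with eligibility and baseline assessment before assignment. The enrolment meant may be entry into treatment. The wording is ambiguous rather than a stated wrong order.
- **That the draw "by a random choice (with replacing) of 20 blocks among the six blocks above defined" contradicts stratification by centre.** It does not. Each block is balanced and drawn independently, so whole blocks can be given to either centre and still form a valid scheme within it.

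The one-third figure is also a ceiling. It falls if patients are randomised in batches, if the clinician sees only some of the earlier arms, or if a centre ends on an incomplete block. Finally, self-report and lack of blinding bear on how outcomes are reported. They are a separate matter from selection at entry.

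**Conclusion.** The point holds as a weakness of the design. With the block size fixed at 4, treatment open, and one clinician both enrolling and announcing arms, up to 33% of allocations (at most about 27 of 80) can be foreseen, and the best guess is right about 71% of the time. Both figures assume a known or inferred block size, full knowledge of the centre's earlier arms, and allocation one patient at a time; with less knowledge or with batching they are lower. A reader might infer that concealment was broken. The article does not show that: it shows that concealment is breakable.

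The matter is worth correcting because the change is cheap and the waiting-list argument does not require a constant block size: under varying sizes, too, each patient can be assigned on arrival.

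**What to change.** **If allocations remain to be made:**

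1. Use a separate list for each centre with randomly varying block sizes, for example 4 and 6, not disclosed to recruiters.
2. State that the statistician holds the list and releases each arm only after consent, baseline assessment and irrevocable registration of the patient. Because varying the sizes barely lowers guessing success, this step matters at least as much as the first.
3. Reword the sentence on the clinician so that enrolment clearly comes before allocation and only the communication of the arm comes after it.

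The cost is a new list, a registration step and a text correction. The downside is a possible within-centre imbalance of 3 instead of 2, since a block of 6 can run three ahead.

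**If the list is already used up** (the article reports the R draw in the past tense): keep the list. For each patient, compute the probability of MIT given the earlier assignments in the block (0, 1/3, 1/2, 2/3 or 1), and test whether baseline DERS is related to it, in the manner of Berger and Exner. Adjust the primary analysis for baseline DERS. An analysis leaving out the determined assignments should be labelled exploratory, as only about 53 patients would remain. The cost is one additional check. A null result would not exclude selection on features that were not measured.

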### Clinical assessment

Independent expert psychologists will conduct the clinical assessment. Clinical evaluation are scheduled at the baseline, after 6, 12 (end of treatment), and 18 months.

The Structured Clinical Interview for DSM disorder [39, 40] will be used to define the diagnosis and collect data on comorbidities.

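### The role in charge of clinical evaluation also passes on the allocated arm, and nothing shown separates that role from the follow-up MAI interviewers or masks them

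*Protocol article*

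**What the plan says.** Three parts of the protocol article bear on this.

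- **Randomization.** Allocation comes after baseline: "After baseline assessments, eligible participants will be assigned to treatment arms". The sequence is in separate hands: "Random allocation will be done by a statistician". The result then reaches the patient by another route, because within two weeks "the clinician in charge for clinical evaluation will enrolled the patients and will communicate the experimental arms". The section's only statement on blinding is that "neither the therapists nor the participants can be blinded for the delivered treatment", with the nature of psychological treatment as the reason. Outcome assessors are not mentioned.
- **Clinical assessment.** "Independent expert psychologists will conduct the clinical assessment". The schedule follows: "Clinical evaluation are scheduled at the baseline, after 6, 12 (end of treatment), and 18 months". The section does not define what the psychologists are independent of, and says nothing about masking.
- **Outcomes.** The MAI is described under Secondary outcomes as "a semi-structured clinical interview aimed to evaluate the metacognitive abilities of patients". Interviewers elicit an account of an emotionally meaningful event and then ask questions to evaluate four subfunctions. The primary outcome, the DERS, is different in kind: "This scale is a 36-item self-report questionnaire".

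**The concern.** Nobody can pass on an allocation without knowing it. The article gives that task to the clinician responsible for clinical evaluation, and it uses the same term, clinical evaluation, for the scheduled outcome visits. The reason offered for not blinding therapists and patients does not extend to assessors, who could be masked in a psychotherapy trial.

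What is at stake is the MAI. It depends on an interviewer's judgement of what a patient says, and metacognition is what MIT is designed to improve. The article's aims and discussion rely on metacognition for the account of how treatment works. A rater who knows that a patient received MIT may, without intending to, hear more metacognitive skill in the narrative. The DERS and most of the other clinical scales described are completed by patients who know their treatment. A masked interviewer rating is therefore one of the main pieces of clinical evidence that could be protected from expectation, and the stated route does not secure that protection.

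**Working it through.** No figure in the plan is in question and no arithmetic decides the point. The check is to set the sections side by side and ask who knows the arm, and when.

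1. **Who generates the allocation?** A statistician (Randomization). This role is distinct from the one that passes the arm on, so the plan already has someone outside the assessments who holds the sequence.
2. **Who learns it next?** The clinician in charge of clinical evaluation, who also enrols the patient (Randomization).
3. **When?** After baseline assessment. Of the four scheduled evaluations (baseline, 6, 12 and 18 months), 4 − 1 = 3 come after the arm is known. The baseline MAI is not exposed.
4. **Who rates the outcomes?** Independent expert psychologists (Clinical assessment). The label differs from the one under Randomization. No section says whether that clinician is one of them, supervises them or stands apart from them.
5. **Is anyone masked?** Randomization says therapists and participants cannot be. The sections on clinical assessment, interventions, outcomes, randomization, and strengths and limitations contain no statement that assessors are masked. Independence from the treating therapist, if that is what is meant, would not amount to ignorance of the arm.
6. **Which outcomes depend on the rater?** The article shows this for the MAI, which it describes as an interview. The DERS is self-report and does not depend on who conducts the evaluation.

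Steps 2, 3 and 4 together give the result. On the plain wording, the evaluation function holds the allocation before every post-randomization evaluation, and the article has no sentence that stops this knowledge from reaching the person who conducts the follow-up MAI.

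The size of the resulting bias cannot be derived. The article gives no standard deviation or target difference for the MAI. The sample-size inputs concern the DERS and cannot be carried over to another instrument.

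**The case against.** The strongest reply is that the two sections describe different people. Randomization speaks of one clinician who enrols patients. Clinical assessment speaks of psychologists, in the plural, and calls them independent. The clinician may be a lead who handles intake, with others rating follow-up unaware of the arm. In that case the fault is one of wording. The article is also a condensed account that points to a SPIRIT checklist in an additional file, so silence about assessor masking is not a fault in itself.

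Much of this stands. A reader might infer that the plan's own procedure unblinds the outcome raters as a matter of fact. The document does not support that, because it never says that this clinician rates any follow-up interview. Nor is the absence of a masking statement the point. The point is the sentence that is present: it gives the allocation to the evaluation role, and the word *independent* elsewhere does not undo it.

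A reader might also extend the point to the ZAN-BPD and the SCID at follow-up. The article does not support that. The ZAN-BPD appears in the shown text only in the legend of Table 1, without its mode of rating. The SCID is described for diagnosis and comorbidity, with no follow-up use stated in the shown text. Nor would it be right to say that masked ratings are the only clinical evidence that could be protected, since hospitalizations and suicide attempts are also recorded.

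**Conclusion.** The point holds as an unreconciled pair of statements with a real consequence for one secondary outcome. As written, the role in charge of evaluation knows the arm before the 6-, 12- and 18-month evaluations, and no shown text separates that role from the MAI interviewers or masks them. The between-arm comparison of the follow-up MAI is therefore open to expectation bias. Its likely direction is in favour of MIT, if raters share the study's hypothesis; that is an assumption. Its size is unknown.

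The reach is limited. Baseline MAI ratings are safe, so analyses that relate baseline metacognition to brain features are not touched. Analyses that use change in the MAI would be. The comparison on the DERS is not affected by who conducts the evaluation, although patients' own knowledge of their arm remains. If the authors can show that the psychologists who rated the follow-up MAI were kept unaware of the arm, only a correction of wording remains.

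**What to change.** **In the Randomization section:** have the statistician release the arm to the assigned therapist, or to existing staff who rate no outcomes, and have that person inform the patient.

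**In the Clinical assessment section:** state that the psychologists who rate the follow-up MAI, and any other interviewer-rated outcome, receive no allocation information. Say also what they are independent of. Ask patients before each follow-up interview not to disclose their therapy, and record the rater's guess of arm at 12 months.

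**For ratings already made:** the Trial status section gives a recruitment start in May 2015 and an expected end in November 2018, so re-routing the message cannot repair completed visits. For each follow-up MAI rating, record whether the rater knew the arm, and report the counts by arm. If enough masked ratings exist, run a sensitivity analysis restricted to them. If not, present the MAI comparison as unmasked and interpret it accordingly.

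**Cost:** a minor change in who passes on one message and one additional case report form item. No new staff are needed, and the sample size and visit schedule do not change. Establishing rater knowledge for past visits takes some retrospective work on study records.
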